## Abstract

**In vitro:**

culturing of endometrial cells obtained from the uterine mucosa or ectopic sites is used to study molecular and cellular signalling relevant to physiologic and pathologic reproductive conditions. However, the lack of consensus on standard operating procedures for deriving, characterising and maintaining primary cells in two- or three-dimensional cultures from eutopic or ectopic endometrium may be hindering progress in this area of research. Guidance for unbiased *in vitro* research methodologies in the field of reproductive science remains essential to increase confidence in the reliability of *in vitro* models. We present herein the protocol for a Delphi process to develop a consensus on *in vitro* methodologies using endometrial cells (ENDOCELL-Seud Project). A steering committee composed of leading scientists will select critical methodologies, topics and items that need to be harmonised and that will be included in a survey. An enlarged panel of experts (ENDOCELL-Seud Working Group) will be invited to participate in the survey and provide their ratings to the items to be harmonised. According to Delphi, an iterative investigation method will be adopted. Recommended measures will be finalised by the steering committee. The study received full ethical approval from the Ethical Committee of the Maastricht University (ref. FHML-REC/2021/103). The study findings will be available in both peer-reviewed articles and will also be disseminated to appropriate audiences at relevant conferences.

**Lay summary:**

Patient-derived cells cultured in the lab are simple and cost-effective methods used to study biological and dysfunctional or disease processes. These tools are frequently used in the field of reproductive medicine. However, the lack of clear recommendations and standardised methodology to guide the laboratory work of researchers can produce results that are not always reproducible and sometimes are incorrect. To remedy this situation, we define here a method to ascertain if researchers who routinely culture cells in the lab agree or disagree on the optimal laboratory techniques. This method will be used to make recommendations for future researchers working in the field of reproductive biology to reproducibly culture endometrial cells in the laboratory.

## Introduction

*In vitro* culturing of healthy and diseased cells is widely used to study relevant pathophysiological molecular and cellular events. These methodologies contribute to the understanding of the molecular mechanisms of disease and the identification of therapeutic targets and biomarkers. *In vitro* cultures bear great potential for further development thanks to recent advances in three-dimensional culture systems, co-culturing methods and organ-on-chip technologies (Valdoz *et al.* 2021, Zhou *et al.* 2021, Hammel *et al.* 2022).

Despite the promise of these methodologies, it is widely recognised that studies can be biased when the primary material is not obtained in a standardised manner or rigorously characterised, potentially resulting in reporting of erroneous observations in model systems that do no longer represent the tissue of origin. Along these lines, data from cell culture repositories indicate that a consistent percentage of cultures used for experimental research contain contaminating species or cell types (Romano *et al.* 2020).

A paradigmatic example in the field of reproductive biology is the use of cell cultures established from the endometrium (uterine mucosa) or endometrial implants at ectopic sites, namely endometriosis or adenomyosis (Khan *et al.* 2015, Wang *et al.* 2015, Cook *et al.* 2017, Maybin *et al.* 2017, Lucciola *et al.* 2020, Romano *et al.* 2020, Rawlings *et al.* 2021, Song & Fazleabas 2021, Yu *et al.* 2021). Among other applications, endometrial cell cultures are frequently used to generate *in vitro* models to study the morphological and molecular basis of embryo implantation. Also, primary cells from ectopic implants are commonly employed as preclinical research models of endometriosis or adenomyosis (Zhang *et al.* 2017, Mc Cormack *et al.* 2021).

There is no consensus on standardised operating procedures (SOPs) for obtaining, characterising or culturing primary cells derived from the endometrium or ectopic lesions. There are also no clear quality standards established or recommended in the current literature. Most laboratories use in-house protocols with little or no harmonisation across institutions or laboratories. A recent systematic analysis of the protocols used to isolate primary endometriotic cells showed that most studies do not reference the methods used, while others isolate endometriotic cells using protocols developed for endometrium, which may incompletely recapitulate ectopic lesions (Romano *et al.* 2020). In addition, the cell lineage and the phenotypic characterisations of primary material are frequently inadequate, thus amplifying the risk of contamination by non-endometrial cells or of culturing dedifferentiated endometrial cells that do not retain an endometrial phenotype. In the case of endometriosis, moreover, despite ample evidence suggesting that different disease subtypes have different or even disparate cellular or molecular signatures/functions, most published studies uses a single lesion type that was most conveniently obtained (in most cases, endometrioma) but generalizes the conclusions to all subtypes of endometriosis nonetheless (Romano *et al.* 2020). Consequently, there is poor consistency in the reported findings across studies and a limited confidence in the reliability of *in vitro* models.

To remedy this situation, the ENDOCELL-Seud (indicated as ‘ENDOCELL’ in the rest of the study) project was designed to solicit expert opinions to determine the validity of different methods used to isolate, culture and characterise primary cells from endometrium, endometriosis and adenomyosis and to establish SOPs (Sinha *et al.* 2011). The ENDOCELL project is based on the Delphi method, an iterative investigation method, which, through a series of evaluation stages aims to bring together the most comprehensive opinion, shared in single statements. The tool is commonly used when a consensus on a specific topic needs to be obtained to fill the gap due to the absence of SOPs or guidelines (Coticchio *et al.* 2021, Braungart *et al.* 2022, Hohmann 2022). The ENDOCELL project aims to provide clear guidance to researchers on unbiased *in vitro* methodologies to further the field of reproductive science. The protocol to harness the opinion of experts and to arrive at consensus opinions on the topics debated is described herein.

### Project oversight ENDOCELL Steering Committee

The project was initiated by the ENDOCELL project coordinator ([name]) and the two facilitators (AR and PV). The project is overseen by the international ENDOCELL steering committee of 12 leading scientists, selected by the coordinator based on publication records and relevant expertise in the field. The ENDOCELL steering committee developed the present protocol, it will follow all phases in the implementation of the protocol and committee members are co-authors of this manuscript. The steering committee works via a series of web-based meetings, which are recorded and can be viewed on demand by committee members. Minutes of the meetings are prepared and circulated. An overview of the ENDOCELL project is outlined in Fig. 1.

**Figure 1 fig1:**
[figure not shown]
Scheme and timeline of the ENDOCELL project. Workflow of the ENDOCELL project related to an example of 1 of the 11 identified methodologies. Stage 1 will last 12 weeks, during which time the steering committee will define the items to be harmonised related to a specific methodology and will prepare the online ENDOCELL survey. During stage 2, four additional weeks will be necessary to define the ENDOCELL working group specific to the methodology. At week 16, the first eDelphi round will be launched and experts will have 4 weeks to respond (until week 20). Data analyses at the end of each round will take 4 weeks; therefore, the third and last eDelphi round will be completed at week 36 (including data analyses). We expect that within an additional 8 weeks the recommendation documents will be ready. Refer to the main text for additional details.

### Stage 1. Identification of methodologies and items to harmonise

The first stage in the ENDOCELL project was to define the *in vitro* methodologies in endometrial research needing harmonisation. The ENDOCELL steering committee identified 11 methodologies for which a consensus is lacking, that is, the establishment and maintenance of (1) primary endometrial cells, (2) normal endometrial cell lines, (3) primary endometriotic cells, (4) primary adenomyotic cells, (5) primary myometrial cells, (6) endometriotic cell lines, (7) epithelial organoids, (8) epithelial and stroma organoid (assembloids), (9) spheroids, (10) 3D culture and cell printing, (11) progenitor stem cells, (12) uterine/endometrial-specific endothelial cells and (13) uterine/endometrial-specific immune cells (Table 1). Subsequently, the steering committee will define items in the methodologies that vary across laboratories. The identification and selection of these items will be guided by the expertise of the committee members together with the outcome of a recent systematic review conducted by the ENDOCELL facilitators, which highlighted critical steps in commonly used *in vitro* procedures (Romano *et al.* 2020). In addition, in compliance with similar initiatives in clinical research (Williamson *et al.* 2017) and translational/basic research (Taylor *et al.* 2008, Bustin *et al.* 2009), the following guiding principles will be considered when evaluating items to be included: (i) reporting of the item should facilitate reproducibility of the studies (i.e. readers should be able to replicate the findings based on the information reported such as culture media and supplements), identifying steps in *in vitro* procedures that influence reproducibility; (ii) reporting of the item should facilitate assessment of the quality of the study and risk of bias, allowing avoidance of experimental errors (i.e. temperatures and timing between tissue collection and culture, phenotypic characterisation of cultures, set of required biomarkers and functional features to ensure cell lineage characterisation and if needed subpopulation definition), (iii) a minimum set of items will be determined for reporting in studies employing cell cultures derived from eutopic and ectopic endometrium, ensuring adherence to data governance standards (i.e. requirements of minimal patients’ data).

**Table 1 tbl1:** Methodologies and items to be harmonised in the ENDOCELL project.

Methodologies	Items	Procedural steps
1. Primary endometrial cells 2. Normal endometrial cell lines 3. Primary endometriosis cells 4. Primary adenomyotic cells 5. Primary myometrial cells 6. Endometriotic cell lines 7. Epithelial organoids 8. Epithelial and stroma organoid (assembloids) 9. Spheroids 10. 3D culture and cell printing 11. Progenitor stem cells 12. Tissue-specific endothelial cells 13. Tissue-specific immune cells	For each methodology, items that varies across labs and introduce risks of bias will be defined. *E.g.: how to dissect primary tissue from patients; what culture media should be used; how to characterise biomarkers, phenotypic and functional features, etc.*	Specific procedural steps related to each item will be defined. *E.g.: Item culture medium: what medium; what supplement; what antibiotics; etc.* This will lead to the development of the ENDOCELL survey

For each item, the steering committee will next identify a series of procedural steps whose definition, reporting and harmonisation are deemed necessary for the guiding principles outlined above to ensure reproducibility, bias assessment and the adoption of minimum standards. For instance, under item ‘culture medium,’ the various kinds of media, supplements, growth factors and antibiotics will be considered (Table 1). Based on the procedural steps identified, the steering committee will create a survey (ENDOCELL survey), consisting of a list of propositions aimed at measuring the consensus for each specific procedural step. For each of the 11 methodologies identified, 1 ENDOCELL survey will be created, with the possibility to combine/merge a number of methodologies into a final single survey.

### Stage 2. Measurement of the consensus across identified methodologies and procedural steps

Consensus will be measured using a three-step Delphi method (Brown *et al.* 2021, Govender 2021), originally designed by RAND corporation in 1950 to create an expert opinion and identify lack of consensus around a specific topic (Claeys *et al.* 2021). The method is based on collecting opinions about specific items from a panel of experts and feeding back anonymously the responses iteratively through several rounds, thus enabling experts to compare the opinions of others together with their own. This method has been extensively used to reach consensus in debated areas of healthcare, ethics, technology and communication. Although variations to the method can be applied, adherence to the Delphi principles is binding: anonymity of responses, iteration and feedback and analysis of the group response. Specifically, for ENDOCELL, we will use an electronic Delphi (eDelphi) method.

### Stage 2a. ENDOCELL surveys

The level of consensus for each procedural step/proposition will be expressed using a 5-point Likert scale (1 = strongly agree, 2 = somewhat agree, 3 = neither agree nor disagree, 4 = somewhat disagree and 5 = strongly disagree), which has already demonstrated consistent outcomes in previous Delphi studies (Akins *et al.* 2005, Vogel *et al.* 2019). A free-text box will be provided for general comments on each item (to justify agreements or suggest wording changes), and a free-text box will be provided at the end of the survey to suggest additional checklist items or provide general comments on the checklist (Colonna *et al.* 2017, Isidori *et al.* 2019). All surveys will be created and administered using Qualtrics (Provo, USA), a user-friendly, feature-rich web-based survey tool that complies to the privacy laws and General Data Protection Regulation.

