### Stage 2b. ENDOCELL Working Group (expert panel)

An additional task of the steering committee will be to define the ENDOCELL Working Group, the panel of experts who will be invited to complete the online ENDOCELL survey(s). The ENDOCELL Working Group will be compiled based on a combination of purposive sampling and literature review-based sampling. PubMed will be searched for all papers published in the last 10 years describing the use of cells/*in vitro* systems. Search terms will be (endometriosis OR endometrium) AND (primary cells OR cell line OR organoid OR* in vitro*) NOT (review). This search will be performed prior to launching the ENDOCELL survey specific to each methodology. First and last authors of the papers will be identified as potential members of the ENDOCELL Working Group and duplicate names/authors will be excluded. The generated list of experts will be evaluated by the ENDOCELL steering committee who will prioritise the identified experts according to their suitability in participating to the survey. The steering committee can also add further names. Members of the ENDOCELL Working Group will be recruited from both academic and industrial sectors.

Depending on the methodology/survey, 150–300 ENDOCELL Working Group members will be invited to participate in the survey. Individuals who wish to opt out of the survey will be removed from subsequent invitations. Participants will be blinded to identities of other individuals in the group, and they will not know the specific answers that other individuals provide. The dropout rate based on previous Delphi studies cannot be foreseen in advance given the wide range reported (20–60%) in the literature (Vogel *et al.* 2019, Mendoza *et al.* 2022).

### Stage 2c. Participation to the ENDOCELL survey eDelphi rounds 1, 2 and 3

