### Stage 3. Data analysis and consensus grading

Data will be analysed by the ENDOCELL steering committee at the end of each eDelphi procedure. Results will be reported as median values of the 5-point Likert agreement scale for each procedural step/proposition in the survey. Consensus will be reached for each procedural step/proposition when the sum of choices 1, 2 and 3 (agree) or 4 and 5 (disagree) reaches 70%. No consensus is reached when the sum of the responses for a negative consensus or a positive consensus is <70%.

The strength of agreement will be measured by the mean absolute deviation from the median (MADM), that is, the average distance of the ratings of each participant from the median, and will be ranked as low (MADM > 1.41), moderate (MADM = 1.08–1.41) and high (MADM < 1.08) (Brown *et al.* 2021).

Stability of consensus at the end of the eDelphi procedure will be reached if the between round group responses varied by ≤10%.

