### Timeline

As outlined in Fig. 1, the creation of the recommendation document for each one of the 11 identified methodologies will proceed through 3 defined stages (identification of items to harmonise – stage 1; three-round eDelphi process involving the ENDOCELL working group – stage 2; data analysis and creation of the recommendation document – stage 3) and will take approximately 44 weeks. More than one methodology may be collapsed into a single ENDOCELL survey when items and procedural steps harmonise and show they are analogous. The progress of the complete ENDOCELL project can be seen on the SEUD webpage (to be further defined).

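### The rating scale has no unable-to-rate answer and the midpoint counts as agreement, so raters who cannot judge a proposition and choose 3 tilt the result towards positive consensus

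*Protocol article*

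**What the plan says.** Stage 2a states: "The level of consensus for each procedural step/proposition will be expressed using a 5-point Likert scale". It sets out the response scale in full: "5-point Likert scale (1 = strongly agree, 2 = somewhat agree, 3 = neither agree nor disagree, 4 = somewhat disagree and 5 = strongly disagree". No further category is described. Each item also has a free-text box, but nothing says that a comment changes how the rating is counted.

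Stage 3 declares consensus "when the sum of choices 1, 2 and 3 (agree) or 4 and 5 (disagree) reaches 70" per cent. The complement is: "No consensus is reached when the sum of the responses for a negative consensus or a positive consensus is <70" per cent. Agreement is also summarised by the median and graded by the mean absolute deviation from the median (MADM): above 1.41 is low, 1.08 to 1.41 moderate, below 1.08 high.

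On who answers, Stage 2b says that "150–300 ENDOCELL Working Group members will be invited to participate in the survey", the number depending on the methodology or survey. Candidates come from purposive sampling and from a PubMed search whose terms are the same for every methodology. The steering committee then ranks them by suitability and may add names. The only opt-out described is from the survey as a whole.

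On merging, Stage 1 allows one survey per methodology "with the possibility to combine/merge a number of methodologies into a final single survey". The Timeline section adds a condition: "More than one methodology may be collapsed into a single ENDOCELL survey when items and procedural steps harmonise and show they are analogous".

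**The concern.** The 70% figure is meant to be a share of expert opinion. Someone who has never used a given technique, and who answers rather than skips, has only the midpoint as a non-committal choice. A 3 can then mean either an informed neutral view or no basis for a view, and the data cannot tell the two apart.

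Because Stage 3 counts 3 as agreement, the second kind of answer does more than add noise. It always adds to the 'agree' total and never to the 'disagree' total. A disputed laboratory step could be recommended as agreed, and a step that informed raters reject could be reported as lacking consensus. Round results are also shown to panellists, who are asked to reconsider in their light, so a distorted total can carry into rounds 2 and 3.

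**Working it through.** The plan gives no figure of its own to reproduce here, so the check applies the Stage 3 rule directly.

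**Inputs**
- Threshold 70%, with 1–3 counted as agree and 4–5 as disagree (Stage 3).
- MADM bands 1.08 and 1.41 (Stage 3).
- u, the share of raters who answer 3 because they cannot judge the proposition. This is an assumption; the documents do not give it. Range shown: 0 to 40%.
- a and d, the shares of informed raters who choose 1–3 and 4–5, with a + d = 1. These are assumptions too. In the worked examples no informed rater chooses 3.

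**Totals under the written rule**
- Agree total = u + (1 − u)a. It reaches 70% when a ≥ (0.7 − u)/(1 − u).
- Disagree total = (1 − u)d. It reaches 70% when d ≥ 0.7/(1 − u).

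| u | informed share needed for 'agree' | informed share needed for 'disagree' |
|---|---|---|
| 0% | 70% | 70% |
| 10% | 0.60/0.90 = 66.7% | 0.70/0.90 = 77.8% |
| 20% | 0.50/0.80 = 62.5% | 0.70/0.80 = 87.5% |
| 30% | 0.40/0.70 = 57.1% | 0.70/0.70 = 100% |
| 40% | 0.30/0.60 = 50.0% | 0.70/0.60 > 100%, unattainable |

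**The same conditions solved for u**
- Positive consensus appears once u ≥ (0.7 − a)/(1 − a): 40% for an even informed split, 25% if 60% agree, 14.3% if 65% agree.
- Negative consensus is lost once u > 1 − 0.7/d: 6.7% for 75% informed disagreement, 12.5% for 80%, 22.2% for 90%.

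**In counts, for 150 completed responses (illustrative; 150 is the lower number invited)**
- Even informed split: 60 unable-to-judge answers plus half of the other 90 gives 60 + 45 = 105, and 105/150 = 70%. This is recorded as consensus to agree.
- 80% informed disagreement with 19 such answers: 0.8 × 131 = 104.8, below the 105 needed. Negative consensus is lost.

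**Strength grading**
- Informed raters split half at 1 and half at 5: MADM = 2.0, graded low.
- Add u = 40% at 3, so the distribution is 30% at 1, 40% at 3 and 30% at 5. The agree total is 70%, the median is 3, and MADM = 0.6 × 2 = 1.2, graded moderate. Complete polarisation among those who know the method is reported as consensus of moderate strength.

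**With unable-to-rate answers excluded**
- The totals equal the informed split at any u. The even split stays at 50%, with no consensus, and the 80% disagreement stays at 80%.

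**If only the pooling of 3 with 'agree' were corrected, so that 'agree' meant 1–2**
- Positive consensus would need 0.7/(1 − u) of informed raters: 87.5% at u = 20%. The direction reverses, but the problem remains.

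**The case against.** The strongest reply is that u may be small. The panel is not simply whatever a general search returns: sampling is also purposive, the committee ranks candidates by suitability, and the Fig. 1 legend allots four weeks to assemble a working group specific to the methodology. Merging is confined to analogous items and steps. At u = 10% the informed share needed for 'agree' drops only from 70% to 67%. All of this stands, and it limits the likely size.

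It is also fair that a condensed article need not describe how the survey handles skipped items. A reader might infer that the survey forces a rating on every proposition. The documents do not support that: nothing says answers are mandatory, and a rater might leave an item blank. How blanks are handled may be set out elsewhere and is not held against the plan here.

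Finally, much of the effect comes from counting 3 as agreement, which is a separate error and applies equally to informed neutral answers. That is correct. But correcting it alone would leave unable-to-judge answers in the denominator, where they would count against positive consensus.

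What the reply does not reach is the ambiguity itself. A rater well suited to a survey may still be unable to judge particular propositions, and none of the safeguards separates that answer from an informed neutral one.

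**Conclusion.** The point holds as a design weakness that is cheap to remove. The scale as stated has no unable-to-rate answer, and the consensus rule turns such answers, when given as 3, into agreement. The bias under the written rule runs one way: towards positive consensus and against negative consensus.

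Its size depends on u, which the documents do not give. It is minor at u = 10% and material from about u = 30% for positive consensus, where 57% of informed raters suffice. Negative consensus is more sensitive: an 80% informed disagreement fails once u exceeds 12.5%. These figures assume that raters who cannot judge choose 3 rather than skip.

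Two stronger readings should not be drawn. One is that unable-to-judge answers could block positive consensus under the present rule. They cannot; that would happen only if 'agree' meant 1–2 alone. The other is that most raters will lack expertise. The documents describe screening intended to prevent that and give no figure either way.

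**What to change.** Before round 1:
- Add an 'outside my expertise / unable to rate' response to every proposition.
- State that this response, and blanks, are excluded from the 70% denominator, the median and the MADM.
- Report the number of raters behind each proposition in every round's feedback and in the final papers.
- In merged surveys, ask one screening question per methodology and show each block only to those who use that methodology.

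Separately, stop counting choice 3 as agreement in Stage 3. Make the two changes together, since either alone leaves a distortion.

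The cost is one extra response option and a routing rule in the online survey tool. The downside is a smaller denominator for specialised propositions, which the reported rater counts will make visible. The change has to precede round 1 because the two meanings of a 3 cannot be separated once the answers are in.
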